### Randomization

After completing the baseline visit and 24 hour diet and physical activity recalls, participants will be randomized to the BA or ST condition. Participants will be stratified into 4 strata of possible combinations of ADM (2: present, absent) × MDD severity (2: Hamilton Rating Scale for Depression (HRSD); [21]: 13–18, 19–24) at baseline. Within each strata, participants will be randomized to the two conditions in randomly permuted blocks of size 3 and 6 using the ralloc program in Stata [22]. This will ensure that the distribution of ADM status and MDD severity are approximately similar between two study conditions.

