### Sample Size Considerations and Statistical Analyses

#### Sample Size

This study will randomize 174 participants into two conditions (87 per condition) who will be followed for 2 years. We expect approximately 90% power for detecting differences in weight between the conditions assuming a weight change difference of 3.1 kg at 1-year (standard deviation = 5.5 kg) and a 25% loss-to-follow-up rate. This projected data for group differences was taken from pilot data at 6 months and projected to one year based on the original DPP weight change data. The standard deviation was a conservative value chosen from a range of successful lifestyle intervention studies [38-40].

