### Primary and Secondary Hypotheses-Analysis Plan

The primary outcome compares body weight between the two randomized groups at 6-months and 1-year follow-up using an intent-to-treat analysis. Linear mixed modeling, using SAS PROC MIXED [41] will test time and group interactions to asses whether within-subject change in body weight differs by condition. Analyses will also be conducted to examine whether there is a dose-response relationship between attendance and outcome, where dose is defined in terms of number of sessions attended. In addition, we will model percent change in body weight at 6-, and 12-months using a similar model.

Secondary outcomes will compare the conditions on depression scores, physical activity, daily caloric intake, treatment adherence (session completion), quality of life score, waist circumference, blood pressure, C-reactive protein and serum lipids at 6-months and 1- and 2-years. Analyses for these outcomes will be similar to those conducted for body weight. To explore proposed mechanisms of change, longitudinal associations of body weight and depressive scores, treatment adherence, and physical activity will be modeled using structural equation modeling [42]. Reciprocal influences of body weight and other factors over time will be modeled in structural equation modeling using nonrecursive models [43]. The two conditions will also be compared on body weight and secondary outcomes at the 2-year follow-up relative to baseline to examine long-term maintenance. The analysis for this outcome will be similar to those conducted for body weight at 6 months and 1-year.

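### Allocation is stratified by antidepressant use and depression severity, but the mixed model as described names only time and group; stating the strata as model terms is a small, free gain

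*Protocol article*

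**What the plan says.** In the Randomization section of the protocol article, "Participants will be stratified into 4 strata of possible combinations of ADM" use (present or absent) and HRSD severity (13–18 or 19–24). The reason given is balance: "This will ensure that the distribution of ADM status and MDD severity are approximately similar between two study conditions". Precision is not mentioned.

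The section Primary and Secondary Hypotheses-Analysis Plan describes an intent-to-treat linear mixed model in SAS PROC MIXED that "will test time and group interactions to asses whether within-subject change in body weight differs by condition". It then says that percent weight change, the secondary outcomes (depression scores among them) and the 2-year comparison will be analysed in a similar way. Neither stratification factor is named in that section. Nor does it say that time and group are the only terms, or that the analysis is unadjusted.

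The Sample Size section states: "This study will randomize 174 participants into two conditions (87 per condition) who will be followed for 2 years". The expected power is about 90%, "assuming a weight change difference of 3.1 kg at 1-year (standard deviation = 5.5 kg"), with "a 25% loss-to-follow-up rate". It claims no gain from stratification or covariates.

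**The concern.** Stratified allocation keeps the arms alike on the stratification factors, so differences between strata add almost nothing to the true sampling error of the treatment effect. A model without the strata still counts that variation in its residual. The reported standard error is then larger than the true one, confidence intervals are somewhat too wide, and the test rejects less often than its nominal level.

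The planned test concerns within-subject change, so only part of the between-stratum variation matters. Stable differences between strata in the level of weight or depression cancel in the change from baseline. What stays in the error is any difference between strata in how much the outcome changes. This also determines what a useful adjustment looks like: stratum main effects alone would do little for the contrast being tested, and stratum-by-time terms are needed.

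The case is clearest for the depression outcomes, because one stratification factor is the baseline HRSD itself, split between 18 and 19, and HRSD is also a secondary outcome. Since one model description serves every comparison between conditions, one clarification covers them all.

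**Working it through.** **Inputs.** From the Sample Size section: 87 per condition, 25% loss to follow-up, difference Δ = 3.1 kg, SD = 5.5 kg, power about 90%. Assumed, because not stated: two-sided α = 0.05 (critical value 1.96), and R², the share of the variance of 1-year change that the four strata explain.

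**1. The plan's own figure.** Completers per arm: 87 × 0.75 = 65.25, taken as 65.

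- SE = 5.5 × √(2/65) = 0.965 kg
- Power = Φ(3.1/0.965 − 1.96) = Φ(1.253) = 89.5%

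With 66 per arm the result is 89.9%. The noncentral t gives 89.0% (65) and 89.5% (66). The stated figure of about 90% therefore reproduces with no stratum adjustment. One-sided α = 0.05 would give 94.2% and does not match.

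**2. Effect of leaving the strata out.** With strata balanced between arms:

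- true SE = 5.5 × √(1 − R²) × √(2/65)
- SE reported without strata = 5.5 × √(2/65)
- actual size without strata = 2 × [1 − Φ(1.96/√(1 − R²))]
- power without strata = Φ((3.1 − 1.96 × reported SE)/true SE)
- power with strata = Φ(3.1/true SE − 1.96)

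Example at R² = 0.10: true SE = 0.915 kg. Size = 2 × [1 − Φ(2.066)] = 3.9%. Power without strata = Φ((3.1 − 1.891)/0.915) = Φ(1.321) = 90.7%. Power with strata = Φ(3.387 − 1.960) = Φ(1.427) = 92.3%.

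| Assumed R² | Actual size, strata omitted | Power, strata omitted | Power, strata included | Gain (points) |
|---|---|---|---|---|
| 0 | 5.0% | 89.5% | 89.5% | 0 |
| 0.01 | 4.9% | 89.6% | 89.8% | 0.2 |
| 0.02 | 4.8% | 89.7% | 90.1% | 0.4 |
| 0.05 | 4.4% | 90.1% | 90.9% | 0.9 |
| 0.10 | 3.9% | 90.7% | 92.3% | 1.6 |
| 0.20 | 2.8% | 91.9% | 94.9% | 2.9 |

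Gains are taken from the unrounded powers (for example 0.9093 − 0.9007 = 0.0086 at R² = 0.05).

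**3. Reading the table.** Both power columns use the same true SE, so they compare like with like. The row for R² = 0.20 illustrates the depression scores. Its power figures carry over the standardized difference planned for weight (3.1/5.5 = 0.56), since the article gives no effect size for HRSD or BDI-II. The calculation treats the comparison as a two-sample test of 1-year change and assumes close balance within strata. Loss to follow-up will loosen that balance, which moves the actual size back towards 5%.

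**The case against.** The strongest reply is that silence is not a statement. A reader might infer that the model contains only time and group and that the strata are ignored. The article does not say so. One sentence names the method and the effect to be tested; it is not a list of terms. A condensed article commonly leaves covariates to the full protocol or analysis plan, which is not at hand. That objection stands: omission is not established, and the point holds only for the model as described.

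Three further objections also stand.

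- The article's stated aim in stratifying is balance. It does not call the factors prognostic for weight and does not count on any precision gain. Its power figure does not depend on the strata.
- If the strata were left out, nothing would be biased and the false-positive rate would not rise. A reader might take wide intervals as a validity problem, but the error is on the conservative side.
- Every R² above is assumed. For weight change it could be close to zero. For the depression scores, a strong link between baseline and follow-up level does not establish that a two-category split explains 20% of the variance in change.

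A reader might also set 91–92% power with adjustment against the roughly 89% obtained when strata explain nothing, and infer a gain of 2 to 3 points for weight at R² of 0.05 to 0.10. That mixes two bases. If the strata explain variance, the unadjusted test under stratified allocation gains some power too, and the like-for-like gain is 0.9 to 1.6 points.

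These objections limit the point but do not remove it. The description as printed leaves open whether the strata enter the models.

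**Conclusion.** A minor point that holds as a free improvement. It is not a demonstrated error. Allocation is stratified on two factors, and the model description that governs every outcome names neither. Run as described, the test for weight would be valid and slightly conservative: actual size about 5.0% to 3.9%, and a power loss of about 0 to 1.6 points, for assumed R² from 0 to 0.10. For change in HRSD and BDI-II the cost may be larger, at about 2.8% size and 3 points of power if R² were 0.20, which is also an assumption.

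The documents do not support reading this as a contradiction, an inflated error rate or a reason to enlarge the trial. The stated power stands as it is.

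**What to change.** In Primary and Secondary Hypotheses-Analysis Plan, state that the mixed models for the primary and secondary outcomes include ADM status (present or absent) and HRSD severity stratum (13–18 or 19–24) as fixed effects, each with its interaction with time. If the full plan already says this, one confirming sentence is enough.

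The cost is negligible. Both factors are recorded before allocation. With baseline, 6 months and 1 year in the model, each two-level factor adds one main effect and two time interactions, so 2 × 3 = 6 parameters against about 2 × 65 = 130 completers. Fixing the terms in advance also removes a later choice between adjusted and unadjusted results. No change to the sample size is needed. A constrained longitudinal model with equal baseline means, or adjustment for the baseline value of the outcome, is a separate and optional choice that this point does not require.

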### Screening Process and Informed Consent

Initial eligibility will be assessed by phone and pre-eligible participants will be invited to the study visit for a screening appointment where informed consent will be obtained and eligibility will be further assessed. The Structured Clinical Interview for the Diagnostic and Statistical Manual-IV [20] will be administered to confirm the diagnosis of MDD. Eligible participants will then complete a baseline assessment visit, for which they will receive $50 (see Table 2 for the list of screening and baseline measures). Those not qualifying will receive referrals to weight loss and/or depression treatment, when applicable.

**Table 2 T2:** List of measures and frequency.

	Screening	Baseline	Month 6	Year 1	Year 2
Structured Clinical Interview for DSM-IV	X		X	X	X
Hamilton Rating Scale for Depression	X	X	X	X	X
Beck Depression Inventory	X	X	X	X	X
Medical History Questionnaire	X		X	X	X
Brief Medication Questionnaire	X		X	X	X
Body weight	X	X	X	X	X
Height	X				
Waist and hip circumference		X	X	X	X
Blood pressure		X	X	X	X
Fasting blood: Cholesterol, LDL, HDL, triglycerides, C-reactive protein		X	X	X	X
Three 24-hour dietary recalls		X	X	X	X
Three 24-hour physical activity recalls		X	X	X	X
Fawcett-Clark Hedonic Capacity		X	X	X	X
Short-form 36 Health Survey		X	X	X	X
Dutch Eating Behavior Questionnaire		X	X	X	X
Paffenbarger Physical Activity Questionnaire		X	X	X	X
Environmental Reward Observational Scale		X	X	X	X

Note. DSM-IV = Diagnostic and Statistical Manual of Mental Disorders, Fourth Edition; LDL = low-density lipoprotein; HDL = high-density lipoprotein

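### The time-by-condition test of change, as described, makes no stated use of the pre-randomization baseline as a covariate or common mean; adding one costs nothing and could sharpen some secondary comparisons, though hardly the weight analysis

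*Protocol article*

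**What the plan says.** Under Primary and Secondary Hypotheses-Analysis Plan, the Protocol article names a linear mixed model in SAS PROC MIXED that "will test time and group interactions to asses whether within-subject change in body weight differs by condition". The same section extends it to other outcomes: "Secondary outcomes will compare the conditions on depression scores, physical activity, daily caloric intake, treatment adherence (session completion), quality of life score", followed by waist circumference, blood pressure, C-reactive protein and lipids. For all of these, "Analyses for these outcomes will be similar to those conducted for body weight". The 2-year comparison relative to baseline is to be handled in a similar way. The section mentions no baseline covariate and no constraint that the arms share a baseline mean.

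Baseline values exist for nearly all of these outcomes. Table 2 has a baseline column that includes, for example, "Three 24-hour dietary recalls", and the Randomization section places them before allocation: "After completing the baseline visit and 24 hour diet and physical activity recalls, participants will be randomized".

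**The concern.** Because baseline is measured before allocation, the two arms have the same expected baseline mean, and any observed difference is chance. A model with time, group and time-by-group terms nevertheless estimates a separate baseline mean for each arm. Its interaction then compares average change, which subtracts the whole of a baseline value that contains measurement error and day-to-day variation. Adjusting for baseline subtracts only the part that predicts follow-up.

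When baseline and follow-up are highly correlated, as is expected for weight, the two approaches nearly coincide. Outcomes built from a few dietary or activity recalls, or from questionnaires, may have lower correlations, and there the change score could give away precision. At stake are wider intervals and a higher chance of missing a real condition difference on secondary outcomes.

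**Working it through.** **Inputs from the documents.** Sample size: "This study will randomize 174 participants into two conditions (87 per condition". Design assumption: "assuming a weight change difference of 3.1 kg at 1-year (standard deviation = 5.5 kg) and a 25% loss-to-follow-up rate". The SD is read as that of weight change. Completers per arm: 87 × 0.75 = 65.25, taken as 65. Alpha is not stated; two-sided 0.05 is assumed. The correlation rho between baseline and follow-up, and the SDs of the secondary outcomes, are not given, so every gain below is a range under assumption.

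**1. The plan's own power.** SE = 5.5 × √(2/65) = 0.965 kg; 3.1/0.965 = 3.213; 3.213 − 1.960 = 1.253; power = 89.5% (89.0% with the noncentral t). The stated figure of about 90% reproduces as a comparison of change scores, with no credit for baseline adjustment.

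**2. Variances of the two analyses, per woman.** With baseline SD s0 and follow-up SD s1:
- change score: s0² + s1² − 2·rho·s0·s1
- baseline-adjusted: s1²(1 − rho²)
- difference: (s0 − rho·s1)², which is never negative

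With s0 = s1 the ratio of adjusted to change variance is (1 − rho²)/[2(1 − rho)] = (1 + rho)/2.

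**3. Weight.** With equal SDs the ratio is 0.90 at rho 0.8, 0.95 at 0.9 and 0.975 at 0.95. Power is Φ(3.213/√ratio − 1.960) = 92.3%, 90.9% and 90.2%, against 89.5%. With a change SD of 5.5 kg, these correlations correspond to baseline SDs of 5.5/√[2(1 − rho)] = 8.7, 12.3 and 17.4 kg. If instead the 1-year SD is 10% larger than an assumed baseline SD of 12 kg (13.2 kg), then rho = (144 + 174.24 − 30.25)/316.8 = 0.909, rho·s1 = 12.0, and the gain is (12 − 12.0)² ≈ 0. The range for weight is therefore about 0 to 3 points.

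**4. Secondary outcomes, completers only, equal SDs.** Start from an effect that the change analysis would detect with 80% power, so that the standardized effect is 1.960 + 0.842 = 2.802. The 80% is a reference point; the article claims no power for secondary outcomes.

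| rho | ratio | power = Φ(2.802/√ratio − 1.960) |
|---|---|---|
| 0.3 | 0.65 | 93.5% |
| 0.5 | 0.75 | 89.9% |
| 0.7 | 0.85 | 86.0% |

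**5. Secondary outcomes, mixed model with dropout.** The completers-only figures flatter the gain, because the planned model also uses women with partial follow-up. Exact generalized least squares variances of the 1-year contrast were computed for visits at 0, 6 and 12 months, equal correlation between visits, and 87 per arm (65 with all visits, 11 with baseline and month 6, 11 with baseline only), in units of the outcome variance:

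| rho | free baseline means | common baseline mean | ratio | 80% becomes |
|---|---|---|---|---|
| 0.3 | 0.0390 | 0.0278 | 0.71 | 91% |
| 0.5 | 0.0285 | 0.0227 | 0.80 | 88% |
| 0.7 | 0.0174 | 0.0153 | 0.88 | 85% |
| 0.9 | 0.00589 | 0.00566 | 0.96 | – |
| 0.95 | 0.00295 | 0.00290 | 0.98 | – |

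**6. Unequal SDs (completers only), rho 0.5.** With s1 = 1.3·s0: change 1 + 1.69 − 1.30 = 1.39; adjusted 1.69 × 0.75 = 1.2675; ratio 0.91; 80% becomes about 83%. With s1 = 1.5·s0: 1.6875/1.75 = 0.96; about 81%. With s1 = 2·s0: 3/3 = 1; no gain.

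**The case against.** The strongest objection is that the article does not fix the parametrization. A test of time and group interactions could equally describe a model with a common baseline mean, and the full analysis plan, which is not shown, may already specify one. This stands in part. A reader might infer that the plan commits to separate baseline means; the text does not say so, and that is only the usual reading of the sentence. The point is not mere missing detail, however. The article does state a method aimed at within-subject change and reuses it across outcomes, and a better use of data already collected can be named.

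The size for secondary outcomes rests on assumed correlations and SDs. This stands. Eligibility caps the depression scores (HDRS at 24, BDI-II at 29) and the HRSD strata run from 13 to 24, so baseline spread is restricted; follow-up spread may be wider, and the gain for depression could be close to nil. Stratification on HRSD severity also limits chance imbalance there.

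Three stronger readings are tempting and are not supported:
- That the primary analysis is underpowered or biased. The stated power reproduces, and the change comparison is valid under randomization.
- That the tests of mechanism are weakened. Physical activity, caloric intake and depression are named mediators, but the article assigns mechanisms to structural equation modeling. Only the condition comparisons on those variables are affected.
- That every listed secondary outcome is affected. Session completion has no baseline value, so the word similar cannot mean one identical model throughout.

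**Conclusion.** The point holds as a modest, free gain in efficiency. If the model is fitted in its usual form, it is in large samples never more precise than a baseline-adjusted or common-baseline model. For weight the difference is about 0 to 3 points of power and changes no conclusion about the design. For secondary outcomes with a modest baseline correlation, the variance of the condition contrast could fall by about 12% (rho 0.7) to 29% (rho 0.3). That range assumes equal SDs, equal correlation between visits and the dropout pattern above. It narrows towards zero as the follow-up SD rises above the baseline SD to s0/rho. No validity error is shown.

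**What to change.** State how baseline enters the model. Either keep baseline in the response vector with one mean common to both arms (time, plus time-by-condition at post-baseline visits only), or model the post-baseline visits with the baseline value as a covariate. Apply this to weight and to each continuous secondary outcome that has a baseline measurement, leaving session completion as a direct comparison of the arms. Report the condition difference with its interval at each visit. If the full analysis plan already does this, the article's description needs only a clarifying sentence.

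The cost is a sentence or two in the analysis plan and a changed PROC MIXED model statement. It needs no new data and no more participants, and it keeps validity under randomization. The structural equation models stay as planned.

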### Study Operation and Tracking System

The tracking system used for monitoring participant study activities and providing necessary prompts is based on a communication system using Lotus Notes software R5 from IBM (Release 5.0.11). Because of its responsiveness to changes in study participants' data, the Lotus Notes tracking system functions as a watchdog for the staff, automatically flagging any participant who is nearing a deadline for a measurement or intervention session. This system is ideal for monitoring the progress of study participants and interventionists, and alerts the project manager and other study personnel to all study data collection points. The software also will be used to gather and store data that can be shared by individuals both on-site and in remote locations. This includes 24 hour dietary and physical activity recall call assignments and the status of these and other data which are collected at remote sites and downloaded directly to the Lotus Notes system. It also provides reports of data such as those from participant questionnaires and blood test results. Storage of such data provides instant access to critical information for intervention and data collection. Multiple levels of password protection are utilized to ensure data security.

### Data Management

All study data are entered into computerized data files utilizing: 1) Lotus Notes for participant tracking and intervention data entry, 2) the Nutrition Data System for Research software computer-assisted telephone interview system for 24 hour recalls, and 3) Snap Surveys for double-entry verification of data from paper and pencil forms. Data sets will be cleaned, verified and archived, and then read into SAS (version 9.1) data sets, which also are archived. All analytic and tracking database files are stored in a secure network drive and backed up at daily basis. On a weekly, monthly, quarterly and yearly basis complete backups are made of all database files. One copy is saved on-site and one off-site. Separate archival databases are permanently maintained.

At the time of data collection, research assistants will review participant responses on questionnaires with participants present. Skipped or incorrectly addressed items will be brought to the participant to correct. Data from pencil and paper forms are entered using a double entry format. All of the data entry systems employ automatic checks for values that are out of range or represent errors of logic. These procedures reduce transcription errors for hard copy data to close to zero (<0.5%). A random 10% of all 24 hour recall telephone interviews will be monitored. Monthly exploratory analyses will be conducted to detect outliers [44].

